$\mu_{0}$ = mean value of outcome variable (HbA1c) at month 12 in the comparison (control) arm

$\left( \mu_{0}-\mu_{1} \right)$ = minimum effect size to be detected

[figure not shown]

[figure not shown]

The necessary sample size for a cluster randomized trial depends on the variation in the intervention effects between the arms, and the clustering due to trial arm allocation (which reduces the variance of the difference between the arms), and the correlation between the repeated observations in each participant. Given that we have a fixed number of health facilities (clusters), to adjust for clustering we used a formula for fixed number of clusters and fixed number of participants within clusters as described in Hemming et al (2011) page 19 [Hemming et al. 2011].

$$Sample size per cluster=\frac{n_{i}*k*\left( 1-\rho\right)}{\left( k-n_{i}*\rho\right)}$$

where: $n_{i}$ = initial sample size

$k$ = number of clusters

= inter-cluster correlation

[figure not shown]

[figure not shown]

It is important to note that each site will be using different numbers of clusters; specifically Uganda will be working in 9 clusters, Sweden in 4 clusters, whereas South Africa will be working in 2 clusters. Thus different inter-cluster correlation (ICC) coefficient values are expected. We were unable to find published literature providing estimates for ICC coefficients for HbA1c among persons with pre-diabetes. We therefore explored various values of ICC coefficients for each site, and used values that provided the highest sample sizes to detect the desired effect size. For Uganda we used an ICC value of 0.200 to obtain a sample size of 112 participants, for South Africa we used an ICC value of 0.044 to obtain a sample size of 129, whereas for Sweden we used an ICC value of 0.06 to obtain a sample size of 79; all per study arm. For Sweden, there will be a further interest to compare the primary outcome of interest between immigrant participants of non-European origin versus immigrant participants of European origin. In order to allow for this sub-analysis, the sample size of 79 for Sweden was doubled to 158 to enable detection of the same effect size between immigrant participants of non-European origin versus immigrant participants of European origin.

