Thus we will aim at maximizing the proportion of participants with diabetes whose blood sugar levels has been reduced, per the criteria defined above. We aim at being able to detect a difference of at least 2% in the percentage of participants with diabetes with reduced plasma glucose levels by month 12 between the trial arms (effect size). The required sample size before adjusting for clustering, at 80% power and 5% level of significance is 58 participants per arm. We have also assumed that in the intervention arm we shall attain reduction in plasma glucose per the criteria given above, in 30% of participants with diabetes (P_1_= 0.3). For this first stage calculations, we used the formula as described in Hayes and Bennett (1999) [Hayes 1999] for proportions, that is:

[figure not shown]

where: $n_{i}$ = initial sample size (58)

$P_{0}$ = Proportion of participants with diabetes in the comparison (control) arm, whose plasma glucose levels are controlled by month 12 (32%)

$P_{1}$ = Proportion of participants with diabetes in an intervention arm, whose plasma glucose levels are controlled by month 12 (30%)

For an estimate of inter-cluster correlation (ICC) among individuals with diabetes, we found only two publications of cluster randomized trials reporting ICC estimates among diabetes patients, one by Littenberg et al (2006) in which they report an inter-cluster correlation (ICC) coefficient for HbA1c among patients with diabetes of 0.055 [Littenberg et al. 2006]; and another by Singh et al (2015) in which they report an ICC coefficient of 0.091 [Singh et al. 2015]. We use some of these estimates. For Uganda we used an ICC value of 0.0.091 to obtain a sample size of 128 participants, for South Africa we used an ICC value of 0.020 to obtain a sample size of 136, whereas for Sweden we also used an ICC value of 0.020 to obtain a sample size of 81; all per study arm.

Once again for Sweden, there will be a further interest to compare the primary outcome of interest between immigrant participants of non-European origin versus immigrant participants of European origin. In order to allow for this sub-analysis, the sample size of 81 for Sweden was doubled to 162 to enable detection of the same effect size immigrant participants of non-European origin versus immigrant participants of European origin.

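### The unsourced ICC of 0.020 behind the South African and Swedish diabetes samples lies below both ICCs the protocol cites, and the site-level 80% power is not supported at the cited values

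*Protocol*

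**What the plan says.** Protocol section 3.10 says the sample was set so that differences in the primary outcomes can be detected at each site separately if wanted.

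**Diabetes.** The base requirement "at 80% power and 5% level of significance is 58 participants per arm", and the aim is to "detect a difference of at least 2% in the percentage of participants with diabetes with reduced plasma glucose levels". Two publications with ICCs among diabetes patients were found. In one, "they report an inter-cluster correlation (ICC) coefficient for HbA1c among patients with diabetes of 0.055"; the other gives 0.091. The text says it uses some of these. Uganda gets 0.091. For the second site, "for South Africa we used an ICC value of 0.020 to obtain a sample size of 136". Sweden also gets 0.020, for 81 per arm, doubled in the text to 162 for a comparison by immigrant origin. Table 16(b) repeats 0.020 for both sites.

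**Pre-diabetes.** No published ICC was found. After noting that the sites have 9, 4 and 2 clusters, the protocol concludes: "Thus different inter-cluster correlation (ICC) coefficient values are expected". It explored various values and "used values that provided the highest sample sizes to detect the desired effect size": 0.200 for Uganda, 0.044 for South Africa, and 0.06 (text) or 0.070 (Table 16(a)) for Sweden.

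**The concern.** The value of 0.020 is neither of the two cited estimates and is less than half the smaller one. With so few clusters, the clustering formula is very sensitive to this input, so the choice largely decides whether the site appears feasible. If a cited value is nearer the truth, a null diabetes result in South Africa or Sweden could be read as adequately powered evidence of no effect when it is not.

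The pre-diabetes text adds two misleading assurances. The ICC describes how alike people within a cluster are for a given outcome and population; it does not depend on how many clusters are sampled. And the remark about the highest sample sizes reads as though a worst case had been taken.

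**Working it through.** **Inputs (Protocol 3.10, Tables 16(a) and 16(b)).** Diabetes base n_i = 58 per arm; pre-diabetes base n_i = 34; two-sided 5%, 80% power; k = 9 (Uganda), 2 (South Africa), 4 (Sweden), all site totals; cited diabetes ICCs 0.055 and 0.091. Sample sizes are those before the 10% allowance for loss to follow-up.

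**Step 1: reproduce the protocol's figures.** Its formula is n = n_i·k·(1−ρ)/(k − n_i·ρ). For diabetes:
- South Africa: 58·2·0.98/(2 − 1.16) = 113.68/0.84 = 135.3, so 136.
- Sweden: 58·4·0.98/(4 − 1.16) = 227.36/2.84 = 80.06, so 81.
- Uganda: 58·9·0.909/(9 − 5.278) = 474.50/3.722 = 127.5, so 128.

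All three agree with the protocol. The clustering arithmetic is right for the inputs chosen.

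**Step 2: change only the ICC.** The formula has a solution only when ρ < k/n_i. That limit is 2/58 = 0.034 in South Africa and 4/58 = 0.069 in Sweden.
- South Africa: both cited ICCs exceed the limit, so no sample size reaches 80%.
- Sweden at 0.055: 58·4·0.945/(4 − 3.19) = 219.24/0.81 = 270.7, so 271 per arm. At 0.091 there is no solution.

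**Step 3: power at the planned size.** Effective size n_eff = n/[1 + (n/k − 1)ρ]; power = Φ(2.802·√(n_eff/n_i) − 1.96). Example, South Africa at 0.055: 1 + 67·0.055 = 4.685; 136/4.685 = 29.0; 2.802·√(29.0/58) − 1.96 = 0.02; Φ = 51%.

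| Diabetes sample (protocol's k) | ICC 0.020 | ICC 0.055 | ICC 0.091 |
| --- | --- | --- | --- |
| South Africa, 136 per arm | 80% | 51% | 36% |
| Sweden, 81 per arm | 80% | 64% | 51% |
| Sweden, 162 per arm | 94% | 75% | 59% |

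In South Africa n_eff cannot exceed k/ρ, which is 36.4 or 22.0. Even unlimited enrolment therefore gives only about 60% or 41%.

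**Step 4: what these figures depend on.**
- *Base size.* For 30% versus 32%, (1.96 + 0.84)²·(0.30·0.70 + 0.32·0.68)/0.02² = 7.849·0.4276/0.0004, about 8,390 per arm, not 58. The percentages above are therefore relative to an unexplained base.
- *Cluster count.* The formula is n = n_i·[1 + (n/k − 1)ρ] solved for n. Since n is per arm, k should be clusters per arm. In South Africa k = 1 puts the limit at 1/58 = 0.017, so even 0.020 has no solution. In Sweden k = 2 turns 81 into 113.68/0.84 = 135.3, so 136.

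**Step 5: the pre-diabetes statements.** The formula rises without limit as ρ approaches k/n_i, so it has no largest value.
- South Africa: 129 at 0.044, but 64.6/0.30 = 215.3 (216) at 0.050 and 64.26/0.13 = 494.3 (495) at 0.055.
- Uganda: 112 at 0.200, but 229.5/0.5 = 459 at 0.250.

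**The case against.** **The shortfall is conditional.** At 0.020, with the protocol's base and k, the formula does return 80%. The cited 0.055 is for HbA1c, while the diabetes outcome is a binary responder, and section 3.10 does not say which measure the 0.091 refers to. The right ICC cannot be known from the document. This stands: a reader might infer that 80% power is simply not delivered, but the document supports only that it is not supported at the ICCs cited.

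**The power figures are not power for the stated effect.** With a base of about 8,390, power at 136 per arm is about 5% even without clustering: Φ(2.802·√(136/8,390) − 1.96). With one cluster per arm in South Africa, between-cluster variation cannot be estimated at any ICC. This also stands. The figures show how far the protocol's own calculation moves with the ICC; they are not the trial's real power. Neither fault rescues 0.020, and correcting k makes the position worse.

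**Pre-diabetes.** A reader might extend the power loss to these samples. That is not established. Even on the base of 34, Sweden's 158 per arm keeps about 81% at 0.091. The stated difference of 3 with SD 2.5 needs 7.849·12.5/9 = 10.9, or 11 per arm, not 34; on that base South Africa's 129 keeps about 96% at 0.091 with the protocol's k.

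**Highest sample sizes.** This may mean the highest among the values tried. Those values are not listed, so on that reading the sentence cannot be checked; it still gives no assurance of conservatism.

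**Site-specific analysis is secondary.** The main plan pools sites, and section 3.13.1 keeps site-by-site comparison as a fallback. That limits the consequence, but section 3.10 still makes the site-level claim.

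**Conclusion.** The point holds for the diabetes samples, as an unsupported assumption and not as an arithmetic slip. South Africa and Sweden rest on an ICC with no source, below both values the protocol found. On the protocol's own base and site-total k, power over 0.020 to 0.091 runs from 80% to 36% in South Africa. In Sweden it runs from 80% to 51% at 81 per arm, or from 94% to 59% at 162. Both Swedish sizes are shown because Table 16(b) prints 81 while the text doubles it. All of this is conditional on the ICC, on n_i = 58 and on k.

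For pre-diabetes the finding is confined to two statements. Cluster counts are not a reason for ICCs to differ; different populations could be, but the protocol does not argue that. And the formula has no highest sample size that could show caution.

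It might be inferred that Uganda's 0.200 should apply everywhere, or that all Swedish and South African results should be called descriptive. The document supports neither: 0.200 is an exploratory value above both cited ICCs, and the three populations are expected to differ.

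**What to change.** In section 3.10 and Table 16(b):
- Give a source or reason for 0.020, or replace it.
- Correct n_i so that it follows from the stated proportions, and use clusters per arm for k.
- Then restate power, or the detectable difference, at planned enrolment for South Africa and Sweden over ICC 0.020 to 0.091. For South Africa, say plainly that one cluster per arm leaves between-cluster variation inestimable.
- Qualify, for the diabetes outcome, the claim that each site can be analysed separately with adequate power.

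In the pre-diabetes text, delete the statement linking different ICCs to different numbers of clusters and the statement about the highest sample sizes.

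The cost is a rewrite of part of section 3.10 and one table. This fix does not call for added participants, but the stated power will be less favourable.

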## 3.11 Quality Control Measures

PROVIDER TRAINING: As a first step in our patient-centered approach, all clinical staff with patient contact will undergo a health care provider training that will last 3 – 5 days depending on the site. The goal of this training will be to standardize the care provided, raise awareness of inadvertent responses that could be stigmatizing to participants, and of possible self-stigmatization among patients, especially when the effects could restrict access to family and community support. Study clinicians and nurses will be trained in adherence counseling; they will be taught strategies for reducing patient risk of non-adherence, identifying and prioritizing problems leading to non-adherence, and building patient self-efficacy for problem-solving and emotional support.

MINIMIZING LOSS TO FOLLOW UP: We will make every effort to minimize loss to follow-up. As part of an incentive for continued participation, participants will have access to the health facility clinics on all working days of the week (Monday to Friday), even outside of their scheduled visits, for the duration of the study period. Participants will be encouraged to use the facility clinic any time they require medical attention. All participants will receive care and services in accordance with standard medical practice available at the health facility.

Further, in our experience it is most helpful to know the participants’ telephone contact information, and the exact location of each participant's residence. This enables study staff to contact participants who miss a clinic appointment, and conduct home visits for participants who miss a clinic appointment by more than one week. Thus a detailed description of each participant's contact information will be recorded at the baseline visit; and this will facilitate future home visits (if necessary). We will collect information on landmark buildings on the way to a participant’s home, the name of the participant’s local community leader, and the participant’s street address (when available). At the time of enrollment, we will ask each participant’s permission to conduct home visits. Regular checks will be made during the follow-up period to determine any residency changes. However, despite our efforts to track participants, some will move without notifying us or will provide an inaccurate address. In these cases, we will pay regular visits to each participant’s home and talk with relatives, neighbors, and friends to determine the participants’ whereabouts. These procedures will be conducted in a culturally sensitive manner without disclosure of information on the participant’s health status or study participation.

ADHERENCE TO STUDY INTERVENTION ELEMENTS: Adherence counseling will occur during the health education and motivational couching sessions that participants will be encouraged to attend. The general health education and motivational couching sessions will occur in morning hours of every clinic day. Further one-on-one health education and motivational couching will be conducted during interactions between the participant and health care workers. Further, treatment adherence counseling will be provided by the pharmacy assistant or adherence nurse-counselor that will include the following: (1) the importance of diabetes treatment adherence, including the adherence level necessary for good treatment outcomes; (2) methods of monitoring treatment outcomes to optimize patient progress; and (3) the patient’s beliefs about the effects of diabetes treatment. The counselor will discuss lifestyle issues (ranging from physical activity, alcohol and tobacco use and diet), explore possibilities for incorporating diabetes and/or lifestyle modification into the participant’s daily schedule, and determine the participant’s motivation and expectations for seeking treatment. Participants will be asked to think about these issues and prepare any questions for their next counseling session. During visits subsequent to treatment, and/ or lifestyle modification initiation, counselors will summarize information presented during previous visits and assess the participant’s confidence in and commitment to long-term diabetes treatment , and/ or healthy lifestyle compliance (using a rating scale of low, moderate, and high). Furthermore for participants with diabetes, the counselor will explore strategies for ensuring that each patient is supported in their home environment while receiving treatment, with encouraging and helping the patient identify a “Care Companion”.

At each health facility, the study staff will help with the establishment of a peer support group for participants with diabetes, that will comprise of patients with diabetes, with a peer group leader being an “expert diabetes patient”. The progress and activities of the peer support groups will be monitored over the course of the study, with support from the study team where needed.

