## 2.2 Specific objectives

### 2.2.1 Primary objectives

The primary objectives of the trial are as follows:

1. To determine the combined effect of the facility+ community strategies, in controlling blood sugar levels among patients with T2D
2. To determine the effect of the facility+ community strategies, in reducing blood sugar levels among individuals with pre-diabetes
3. To determine the effect of the facility+ community strategies, on retention into care among patients with T2D.
4. To estimate the incremental provider cost per patient of managing patients with T2D, as a result of implementing the facility+ community strategies.
5. To estimate the incremental client cost per patient of managing patients with T2D, as a result of implementing the facility+ community strategies.

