## 3.2 Study Arms:

Sweden and South Africa will use two study arms, one with facility only interventions as the control condition, and a second arm with facility plus community interventions. The intervention elements in each of these arms are described later in section 3,3.

In Uganda, because the proposed facility only interventions are not yet standard of care in the country, a third arm that will comprise of “current practices” in the prevention and management of type 2 diabetes will be used against which the effectiveness of facility only, and the that facility+ community intervention arms will be compared.

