Community mobilization is designed to raise awareness of type 2 diabetes and it’s prevention and management through healthy lifestyle, timely seeking of care and self-management of the disease. It will be used to raise interest in participation in the trial, and it will also help to create and strengthen advocacy for healthy lifestyle in the communities, thereby supporting the goals and activities of the Peer group program, Care Companions / Healthy Lifestyle Buddies and Community Link Team. Key messages for community mobilization will address knowledge gaps identified in the formative research, and they will be compiled in collaboration with relevant stakeholder organizations. Materials for community mobilization will include one-pagers with the key messages and/or visuals. They will be distributed in the Health Facility + Community arm at community screening events, and through partner organizations, Community Link Team, and Peer groups.

*Community Strategy II: Strengthening support from the environment*

This strategy includes strategies for both social and physical environment. ***Peer group program*** will provide an arena for emotional support, practical support and information exchange for individuals living with diabetes and pre-diabetes. Participants in the Health Facility + Community arm are referred to a peer group in their first motivational coaching session. Peer groups meet monthly at a local community venue under the leadership of appointed ***Expert patients*** and co-leaders selected from within each group. A generic ***SMART2D Peer Group Program manual*** (see Appendix) includes topics and activities for 1) building rapport; 2) setting agenda for the group; 3) working with topics selected by the group; 4) receiving and giving ongoing support; and 5) evaluation and adjourning. In addition to the activities, each group meeting will include a brief physical activity break and opportunity for unstructured discussion and sharing. Peer groups are also open for family members and Care Companions / Healthy Lifestyle Buddies. ***Selection criteria*** and recruitment of Expert patients as Peer group program facilitators are outlined in the ***Peer group program manual*** (refer to Appendix). Peer leaders will be asked to give a written commitment for taking the role; in return they will get training, a SMART2D Peer leader certificate, a fixed budget for meeting-related expenses, and a small compensation for each group meeting.

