**Recruitment of care companions screening (*to be answered by the patient*)(**[**Knowlton 2003**](#_ENREF_1)**)**

1. Who would you prefer to help you out if you needed help? E.g if you couldn’t take care of yourself, who would you want to stay with?
2. Who do you think will be the most helpful person in your life in dealing with Diabetes/prediabetes?
3. Is there anyone else who would be especially helpful with dealing with diabetes/prediabetes?

**Criteria for selection (*information for clinicians*)(**[**Nachega, Chaisson et al. 2010**](#_ENREF_3)**,** [**Kunutsor, Walley et al. 2011**](#_ENREF_2)**)**

1. Must be living in the patients’ household/neighborhood
2. Aware of patients’ health condition
3. Has accepted patients’ health condition and is a confidant
4. Willing and committed to support patient with care for a long period of time
5. **ROLE OF CARE COMPANIIONS**
6. Remind patients to go for next clinic appointments and peer group sessions.
7. Remind patients to take diabetes medication; observe and record while patient takes at least one dose per day?([Nachega, Chaisson et al. 2010](#_ENREF_3)).
8. Observe and confirm that daily/weekly physical activity goals are met.
9. Ensure a healthy diet for the patient.
10. **TRAINING GUIDELINES**

Patients and their selected care companions will undergo 90 minutes of baseline training on;

1. Diabetes/ prediabetes (causes, diagnosis, signs and symptoms, treatment and control)
2. Diabetes/prediabetes lifestyle (physical activity, diet)
3. Role of care companions

Care companions will receive booster health education every 3 months

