**SHOW CARD 7: Responses (sections 13-18)**

**(Give the SHOWCARD to the participant so it will be easier for him/her to respond to the questions)**

| **1 Strongly disagree**  **2 Disagree**  **3 Neutral**  **4 Agree**  **5 Strongly agree**  **888 Not applicable** |
| --- |

1. In Health Facility and Community arm only [↑](#footnote-ref-1)

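### Section 3.11 puts peer groups at every facility and exempts no arm from training, coaching or tracing, contrary to the arm definitions in sections 3.2 and 3.3

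*Protocol*

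**What the plan says.** **Peer groups.** Section 3.11, under adherence to the intervention elements, reads: "At each health facility, the study staff will help with the establishment of a peer support group for participants with diabetes". The leader is to be an expert patient, and the study team monitors and supports the groups. Section 3.3.3.1 reads: "Participants in the Health Facility + Community arm are referred to a peer group in their first motivational coaching session". Table 8 lists the peer group programme among the strategies of that arm. The footnote to Table 2, attached to expert patients and peer groups, reads: "In Health Facility and Community arm only".

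**Training and coaching.** Section 3.11 says that "all clinical staff with patient contact will undergo a health care provider training", lasting 3 to 5 days, and puts education and coaching sessions on every clinic day, with one-to-one coaching besides. Section 3.2 adds a third, current-practice arm in Uganda "because the proposed facility only interventions are not yet standard of care in the country". The data collection tool codes that arm as no intervention. Section 3.3.2.3 confines Ugandan coaching to groups at months 3, 6, 12 and 18.

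**Tracing.** Section 3.11 has study staff contact participants who miss a clinic appointment and "conduct home visits for participants who miss a clinic appointment by more than one week". No arm is named. Primary objective 3 in section 2.2.1 is the effect of the facility + community strategies "on retention into care among patients with T2D".

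**The concern.** Section 3.3 says that the trial is to isolate what a community component adds to optimal facility care. Peer groups led by expert patients are a main part of that component. If site staff set them up wherever there is a participating facility, the controls receive part of what is being tested, and no analysis can undo that afterwards.

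In Uganda the third arm exists to show what happens without the facility package. Training its staff and coaching its patients would change the practice that the arm is meant to represent.

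Retention in care is a primary objective. If study staff bring back patients who miss appointments in every arm, part of the observed retention is produced by the study rather than by the assigned strategies.

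**Working it through.** The protocol gives no figure on this point, so the check sets the intended scope of each measure beside its scope in section 3.11.

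| Measure | Intended scope | Scope in section 3.11 | Consequence |
|---|---|---|---|
| Expert-patient peer groups | Facility + Community arm only (3.3.3.1, Table 8, Table 2 footnote) | Each health facility, participants with diabetes | Contradiction; reaches the facility-only arm and Uganda's third arm |
| Staff training | Part of the facility strategies (3.3.2.2, Table 4), so facility-only and Facility + Community | All clinical staff, no arm named | Contaminates only Uganda's third arm |
| Motivational coaching | Facility Strategy II (3.3.2.1, Table 2), so the same two arms | Every clinic day and one-to-one, no arm named | Contaminates only Uganda's third arm; schedule conflicts with 3.3.2.3 |
| Tracing of missed visits | In Uganda, telephone to the patient and then through the care companion, as a facility element (Table 5) | Contact and home visits by study staff, no arm named | Overlays the assigned tracking and acts on retention |

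**Peer groups.** The sentence in section 3.11 is not a plain restatement of section 3.3. It describes groups of patients with diabetes, whereas Table 8 specifies mixed groups with pre-diabetes in Uganda. A reader therefore cannot assume that it inherits the arm restriction.

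**Coaching in Uganda.** Every clinic day plus one-to-one sessions cannot be squared with groups only, at four named months. Month 18 also lies beyond the 12-month follow-up in section 3.8. Training lengths differ too: 3 to 5 days in section 3.11, against half-day or one-day sessions in Table 4.

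**Retention.** Section 3.8 has participants with diabetes attend monthly. Table 8 adds, in Uganda's community arm, reminders from peer leaders to attend visits. Study tracing thus acts on the same behaviour as both the facility tracking and the community reminders. Applied equally, it can be expected to raise retention in every arm and narrow the difference. Section 3.9 lists no retention outcome, so the protocol does not say whether attendance after a tracing contact counts.

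**Size.** Let q be the share of controls who take up a peer group and s the share of the community effect that runs through peer groups. On a simple dilution model the contrast shrinks by c = q × s. From the nominal 80% power at two-sided 5% (section 3.10), used only as a reference point:

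- power = Φ((1 − c)(1.960 + 0.842) − 1.960), and required n grows by 1/(1 − c)²
- c = 0.10: power 71%, n × 1.23
- c = 0.25 (for example q = 0.5 and s = 0.5): power 56%, n × 1.78
- c = 0.50: power 29%, n × 4.0

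Both q and s are assumptions; the documents give neither. The list shows sensitivity and does not estimate the loss in this trial.

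**The case against.** The best defence is that sections 3.3.2 and 3.3.3, with their tables and footnote, define the arms in detail, so that each facility in section 3.11 can be read as each facility with a community component. That is probably the intention. But the sentence carries no such limit, and the paragraph before it describes coaching that belongs to both main arms. Site staff working from section 3.11 would have no reason to leave control facilities out.

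Tracing also has a proper purpose. It limits loss to follow-up for the month-12 HbA1c outcome, for which 10% loss is assumed, and eligibility requires agreement to home visits. That stands, and it is a reason to keep tracing and record it rather than to stop it.

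Several stronger readings are tempting, but the documents do not support them:

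- **The controls receive the whole intervention.** They do not. Community mobilisation, link teams, environment work and the extra care-companion tasks stay in the community arm.
- **Training and coaching contaminate the facility-only arm.** They are part of its design, and that arm is the only comparator in Sweden and South Africa.
- **Every primary comparison is affected.** The peer-group sentence covers participants with diabetes only. It leaves the pre-diabetes HbA1c comparison between the two main arms untouched.
- **Appendix 5.2 gives all care companions the community tasks**, such as "Observe and confirm that daily/weekly physical activity goals are met". The appendix names no arm, but section 3.3.3.1 cites these guidelines within its account of the Facility + Community arm, Table 8 lists the guideline there, and section 3.3.3.3 says that guidance for the role is given in the community arm.
- **Retention becomes inestimable.** Tracing applied alike in all arms leaves a between-arm difference that can be estimated, though probably a smaller one.
- **The multipliers above are the trial's sample-size need.** They hold only for an assumed c.

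**Conclusion.** The point holds in a limited form. The peer-group sentence in section 3.11 contradicts section 3.3.3, Table 8 and the Table 2 footnote. If followed, it biases the diabetes comparison towards no difference by an amount that the documents do not allow to be calculated. Training and clinic-day coaching without an arm restriction compromise Uganda's current-practice arm and no other, and the Ugandan coaching schedule is stated in two incompatible ways. Tracing in all arms attenuates the contrast for primary objective 3 but leaves it estimable. These conclusions assume that sites follow section 3.11 as written and, for retention, that tracing is applied equally across arms.

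**What to change.** 1. Limit the peer-group sentence in section 3.11 to Facility + Community facilities, so that it agrees with section 3.3.3.
2. Limit the training and coaching in section 3.11 to arms assigned the facility strategies, and say expressly that Uganda's current-practice arm is exempt.
3. Reconcile the coaching schedule in section 3.11 with section 3.3.2.3, and the training length with Table 4. Which schedule or length applies is for the investigators to settle.
4. Keep the tracing, log each contact by study staff with its date, and score retention in care from attendance recorded before any such contact.

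The cost is a wording change, an instruction to sites, minor record-keeping and a slightly stricter retention measure. Patients who miss routine appointments are still followed up.
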